## Abstract

**Background:**

Romantic relationships play a critical role in adolescent development, and by middle adolescence, most young people have been involved in at least one romantic relationship, a context in which most sexual interactions occur. Research suggests adolescents lack positive models and skills related to building healthy relationships.

**Objective:**

This project aims to test the impact of an innovative healthy relationships intervention, called About Us, implemented in school-based health centers (SBHCs) in California in a randomized controlled trial.

**Methods:**

About Us is being tested using a 7-site, 2-group, parallel randomized controlled trial with a treatment versus control allocation ratio of 3:2 to assess the impact of the intervention relative to the standard of care among adolescents aged 14 to 18 years. Adolescents with active parental consent provide study assent at each of the 3 survey time points: baseline, 3 months postintervention, and 9 months postintervention. A stratified randomization procedure was used to ensure balance in key covariates and screening criteria across intervention groups. Through benchmark intent-to-treat analyses, we will examine the primary outcome of this study—the impact of About Us relative to the standard of care 9 months following the end of the intervention on the prevalence of vaginal or anal sex without condoms in the past 3 months. The secondary outcomes are four-fold: what is the impact of About Us relative to the standard of care 3 and 9 months following the end of the intervention, on (1) the prevalence of abstinence from vaginal or anal sex in the past 3 months, (2) composite scores of relationship communication and positive conflict resolution among participants involved in a relationship at baseline, (3) the prevalence of SBHC service use or information receipt in the past 3 months, and (4) composite scores of condom use intentions and attitudes regarding condoms and other birth control? Additionally, as part of our sensitivity analyses, two additional analyses will be implemented: modified intent-to-treat and complete case analysis.

**Results:**

This project (ClinicalTrials.gov #NCT03736876) was funded in 2016 through the Family Youth Services Bureau as part of the Personal Responsibility Education Innovative Strategies program. Baseline data collection took place between February 2018 and March 2020, yielding a total of 5 cohorts and 533 study participants: 316 assigned to treatment and 217 assigned to control. Ongoing follow-up data collection continued through May 2021.

**Conclusions:**

About Us draws on developmental science to create a contextually and developmentally relevant program that addresses motivation and emotional influences in sexual decision-making. The intervention was designed for implementation within SBHCs, an understudied venue for relationship and sexual health promotion interventions. Unfortunately, COVID-19 pandemic restrictions led to school closures, interrupting ongoing programming, and in-person follow-up data collection, which has affected study attrition.

**Trial Registration:**

ClinicalTrials.gov NCT03736876; https://clinicaltrials.gov/ct2/show/NCT03736876

**International Registered Report Identifier (IRRID):**

DERR1-10.2196/30499

## Introduction

### Background and Rationale

Romantic relationships play a critical role in adolescent development [1]. By middle adolescence, most young people have been involved in at least one romantic relationship [2], a context associated with greater odds of sexual intercourse [3] and in which most sexual interactions occur [4]. Research suggests adolescents lack positive models as well as norms and skills related to building healthy relationships [5]. Nonetheless, developmental psychologists emphasize that adolescence represents a new period in which past models of relationships may be reshaped, priming young people for healthier adult relationships [6]. Additionally, research suggests adolescents’ views on relationships may be influenced by discussions with peers [7], highlighting the importance of promoting positive normative beliefs and sexual behavior within the context of relationships.

Opportunities for sexual experimentation and status attainment are often at the forefront of adolescents’ initial views of romantic relationships [8], providing leverage points for interventions to guide adolescents in setting sexual boundaries and identifying potentially unsafe sexual situations. Accordingly, adolescents with experience in relationships are primed for prevention programs that address critical relationship skills, such as communication in intimate relationships and navigating different sexual boundaries. Using a targeted approach that involves identifying and engaging adolescents with increased vulnerabilities maximizes resources and prioritizes serving them. This project centers on promoting healthy relationships and expanding the typical prevention education foci in sexual health.

Focusing on romantic relationships aligns with developmental science underscoring the importance of relationships in adolescence. Because of continued disparities in sexually transmitted infections (STI) and unintended pregnancies in the United States, there remains a need for addressing pregnancy and disease prevention. Among adolescents aged 15 to 19 years, the teen birth rate declined 7% from 2017 to 2018, from 18.8 to 17.4 births per 1000; however, the teen birth rate remained approximately twice as high for Hispanic and Black teens compared to non-Hispanic White teens [9]. Additionally, 75% of teen pregnancies are unintended [10,11]. Further, rural counties observe higher teen birth rates compared to urban and suburban areas [12]. Very few evidence-based program models addressing sexual risk have been developed and tested with targeted populations, such as Hispanic adolescents or those residing in more rural areas [13,14].

Not all young people are at equal risk of experiencing an unplanned pregnancy or STI. Indeed, some contextual factors, such as experience with romantic relationships or even exposure to violence, place adolescents at greater risk for engaging in sexual activity, including unprotected (eg, condomless) sex that could lead to an unplanned pregnancy or STI. In addition, exposure to violence, both directly and indirectly, is associated with risky behaviors (eg, unprotected sex), lack of self-efficacy, anxiety, depression, challenges developing and maintaining healthy relationships with prosocial peers, and increased associations with peers who endorse unsafe norms and behaviors [5,15]. Estimates suggest that 60% of children and adolescents younger than 18 years have been exposed to at least one form of violence in the previous year [16], meaning these adolescents are at increased vulnerability for other poor outcomes.

Most existing evidence-based programs (EBPs) for adolescents are delivered in community-based settings or schools (eg, Making Proud Choices; Reducing the Risk) [17,18]. A few are delivered through health clinics (eg, Seventeen Days) [19], but none to our knowledge have been developed and tested expressly for implementation via school-based health centers (SBHCs). SBHCs are clinics initially created in response to adolescent health needs that operate on or near school campuses and provide a range of age-appropriate health-related services to adolescents. Today, most SBHCs also offer a comprehensive array of services, including primary care, mental health services, and health education. In most high school SBHCs, reproductive health is a core service [20]. As SBHCs become more common across the United States, the role SBHCs play in prevention and health promotion interventions will also grow in importance [21]. SBHCs are uniquely positioned, both physically and philosophically, to reach young people. SBHCs’ location on or near a school campus offers easy access to large groups of adolescents. More importantly, however, SBHCs focus on building trust and meeting young people “where they are” developmentally. Thus, SBHCs offer a unique opportunity to deliver health interventions that integrate prevention education and clinical care [20].

This original paper outlines the rigorous evaluation of About Us, an innovative healthy relationships intervention implemented in SBHCs to reduce the prevalence of unprotected sex and promote stronger relationships among adolescents facing disparities in sexual health outcomes.

### Intervention

Developed from a piloted intervention, About Us is an innovative healthy relationships intervention that promotes positive adolescent romantic relationships, condom use, and highly effective contraceptives if participants are having sex. The program includes 10 lessons (2 lessons are 30-45 minutes long and 8 are 50 minutes long) that blend group-based activities with online activities implemented in a small group format with students in grades 9 or 10 who have parental consent and provide assent to participate.

About Us draws on the latest research on developmental neuroscience to shape content and strategies. Part of the innovative design of About Us stems from the use of positive youth development (PYD) principles and adolescent development literature as core elements that are foundational to the curriculum. PYD is a strength-based approach used to promote adolescents’ prosocial competencies and skill-building related to their positive health and well-being [22]. The adolescent development literature, such as that reported by Collins [23], guides the relationship development content and helps ensure it is age-appropriate.

The program also draws on dual-process theories to address socioemotional well-being and cognitive influences on sexual decision-making [24]. For example, in a lesson on correct and consistent condom use, the program addresses adolescents’ explicit intentions to use a condom during sexual intercourse and has them explore which circumstances might precipitate their decision to have sexual intercourse without condoms, prompting them to recognize and navigate these experiences to avoid condomless sex. Finally, the program draws from social cognitive theory [25], both in terms of key constructs in skill acquisition, such as building self-efficacy or confidence in one’s ability to perform a behavior and shaping the process of learning through observational learning or modeling during instruction. Bandura [25] posited that self-efficacy is influenced in 4 ways: mastery experiences (successful completion of a task), modeling (observing others similar to oneself perform a task successfully), social persuasion (information from others that one can perform a task successfully), and physiological arousal states (information from one’s physiological state, such as anxiety). The program draws on these strategies in the skills-based sessions to maximize its impact on self-efficacy. For example, to apply the concept of mastery experiences, the program includes role-play exercises in which adolescents practice in context (small groups and online) and receive feedback on their use of the skills.

Each About Us session includes an initial soap opera-like story to build interest and illustrate key concepts, 2-3 group-based activities with reflection, individual app-based work on computer tablets (to allow for personalization of the content), and a group-based debrief to reflect on the session and reinforce key messages. To maximize the relevancy of the content and strategies, we engaged adolescents in developing the About Us curriculum, and they contributed to its naming, cast of characters, and storylines.

For this study, the group-based content was delivered by trained facilitators (eg, health educators) from participating SBHCs. The app-based content was housed on a secure website and accessed through tablets with unique logins for each participant. Online activities were completed individually during each session (eg, completing a poll or watching and responding to a brief video). Several lessons also included homework activities that encouraged communication between students and a caring adult. Additional details of About Us are displayed in Table 1.

Participants assigned to the treatment group attended group sessions at the designated space. Health educators followed up with students who missed a session to engage them and remind them of the next session. Participants assigned to the treatment group received a US $30 incentive if they attended 6 or more sessions.

**Table 1 table1:** About Us intervention components.

Component	Amount, duration, and intended dosage	Content	Who delivers	Setting
Group-based sessions	10 (2 prelessons and 8 regular lessons) over 4-9 weeks for a total of 10 hours of programming.	Characteristics of healthy and unhealthy relationships, communication skills (having difficult conversations, such as sexual consent, sexual boundaries, and condoms; using “I” statements); personal and sexual boundaries and sexual consent; condom and contraceptive use; influences on sexual decisions in relationships; ending relationships.	Trained health educators from the school-based health centers.	During school (students pulled out of class to come to the health center or other agreed-upon space on the school campus).
Online work during regular group-based sessions	Approximately 15 minutes in each regular lesson; students are able to revisit content from prior lessons outside of group sessions during the implementation period.	Same as above; online activities allow for the review and application of key concepts and the personalization of content for each lesson.	Trained health educators from the school-based health centers will prompt and support students using the tablets and the application during the group sessions.	Same as above.
Parent/other adult-adolescent homework	2 homework activities.	Brief conversation-based homework activities focused on healthy relationship values and influences related to sexual expectations in relationships.	Trained health educators “assign” homework activities as part of the group-based sessions; adolescents are asked to bring back a sign-off sheet acknowledging they completed the activity, which will be included in the implementation log.	These were assigned during the program implementation, but the setting for completion was out of school.

### Study Objectives

The overall goal of this project is to test the impact of the About Us blended learning healthy relationships intervention, implemented in SBHCs in a randomized controlled trial (RCT), on reducing unintended pregnancies and STI in adolescents facing disparities in sexual health outcomes.

### Research Questions and Hypotheses

During the 9 months following the end of the program, what is the impact of About Us relative to the standard of care on the prevalence of vaginal or anal sex without condoms in the past 3 months? We hypothesize that at the final follow-up, the prevalence of self-reported unprotected vaginal or anal sexual intercourse (ie, without condoms) in the past 3 months will be lower among adolescents in the intervention group than students in the control group.During the 3 months and 9 months following the end of the program, what is the impact of About Us relative to the standard of care on (1) the prevalence of abstinence from vaginal or anal sex in the past 3 months, (2) composite scores of relationship communication and positive conflict resolution among participants involved in a relationship at baseline, (3) the prevalence of school-based health center service use or information receipt in the past 3 months, and (4) composite scores of condom use intentions and attitudes regarding condoms and other birth control? At each follow-up, we hypothesize that, compared to the control group, students in the intervention condition will have: (1) a higher prevalence of sexual abstinence in the past 3 months, (2) higher composite scores showing stronger relationship communication and more positive conflict resolution (3) a higher prevalence of SBHC services utilization or information receipt, and (4) higher composite scores showing stronger intentions and more positive attitudes regarding condom use and other forms of birth control.

## Methods

### Study Design Overview

This study is a 7-site, 2-group, parallel RCT with a treatment versus control allocation ratio of 3:2, assessing the impact of the About Us program relative to the standard of care among adolescents aged 14 to 18 years. Figure 1 summarizes study screening, eligibility assessments, enrollment, randomization, and follow-up results.

**Figure 1 figure1:**
[figure not shown]
CONSORT diagram for the About Us evaluation (as of October 2020).

### Study Funding and Ethics Approval

This study was funded in 2016 through the Family Youth Services Bureau (FYSB) as part of the Personal Responsibility Education Innovative Strategies (PREIS) program as an award to ETR. This project was approved by the San Diego State University (SDSU) institutional review board (IRB) in March 2017. In June 2020, Indiana University approved an IRB reliance (protocol 2004100675) on the SDSU IRB approval (protocol HS-2017-0121). The study is registered with clinicaltrials.gov (NCT03736876).

### Study Setting

This project was implemented in 7 SBHCs in rural or suburban communities throughout California with large Hispanic populations. The California School-Based Health Alliance (CSHA) assisted the About Us project team in recruiting participating sites and supporting the clinic screening process used as part of assessing eligibility. The CSHA supports the entire network of SBHCs in California.

### Eligibility Criteria

Students in the 9th and 10th grades between the ages of 14 and 18 years were eligible to participate if they met at least one of two eligibility criteria: (1) had ever witnessed a serious injury or homicide or (2) had a girlfriend, boyfriend, or partner before or during the study consent process (prior or current experience with a romantic relationship). In addition, a student would be considered ineligible if a sibling or step-sibling had already enrolled in the study to avoid contaminating participants in different conditions.

### Recruitment

#### Power Analyses

For a statistical power of 80%, to detect a 9% difference (effect size: prevalence ratio=0.74, 95% CI 0.60-0.91 equivalent to an odds ratio [OR] of 0.65 or Cohen’s *d*=0.24) in the prevalence of condomless sex at 9 months between intervention and control group participants with an allocation ratio of 3:2, we needed to have a sample size of 508 and 339 subjects in the intervention and control groups, respectively, based on a simple two-tailed proportion difference test at a Type I error of 5%.

We selected a minimum detectable effect of Cohen’s *d*=0.2. The rationale for this selection is two-fold: (1) in our R21 pilot test of a less robust version of the About Us curriculum with a very small (<100) sample, we achieved an estimated effect size of *d*=0.15 for our unprotected sex outcome, and (2) in a meta-analysis of group-based pregnancy or STI interventions, the average effect size across multiple studies was OR 0.70, which corresponds to a small Cohen’s *d*=0.19 [26,27].

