### Baseline Data Collection

At the time of assent and prior to randomization, adolescents completed the baseline survey on a self-administered tablet device via the Qualtrics Offline Surveys application (version 1.4.06) [28]. Following survey administration, EDCs promptly uploaded responses to the QualtricsXM server as soon as a secure internet connection could be achieved. EDCs were provided Verizon Jetpack MiFi devices (7730L and 8800L) for this purpose.

Participants were enrolled and completed baseline surveys on a rolling basis during the spring and fall semesters of 2018 and 2019 and spring of 2020. The targeted enrollment was approximately 173 students per site over 5 semesters (34 to 35 students per semester) for a total of 865 students.

At the completion of baseline surveys for a given cohort at a given site, the EDCs submitted a baseline survey administration log to the evaluation project manager for review and transferred data to the evaluation statistician for randomization into either About Us (intervention) or standard of care (control).

Baseline data collection consisted of two separate instruments: a computer tablet-based survey designed to capture adolescent knowledge, attitudes, and experiences regarding sexual behavior, contraception, STI, and HIV/AIDS; and a brief survey that collected contact information for study follow-up purposes. EDCs were selected and trained by the evaluation team to represent the study in the local communities and schools within which About Us was being implemented and evaluated.

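### The sample size is calculated for d=0.24 but the stated minimum detectable effect is d=0.2, and the enrollment target of 865 fits 5 sites, not the trial's 7

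*Protocol article*

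**What the plan says.** Protocol article, Power Analyses, first paragraph: the calculation is introduced with "For a statistical power of 80%, to detect a 9% difference", and that difference is described as "effect size: prevalence ratio=0.74, 95% CI 0.60-0.91 equivalent to an odds ratio [OR] of 0.65 or Cohen’s *d*=0.24". The result is 508 intervention and 339 control participants (847 in total), at 3:2 allocation, with a two-sided 5% test of two proportions.

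Second paragraph of the same section: "We selected a minimum detectable effect of Cohen’s *d*=0.2". Two reasons follow. The pilot of a less developed curriculum gave d=0.15 for unprotected sex, and a meta-analysis of group-based interventions gave an average OR of 0.70, which the article converts to d=0.19.

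Baseline Data Collection: "The targeted enrollment was approximately 173 students per site over 5 semesters (34 to 35 students per semester) for a total of 865 students".

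Study Design Overview: "This study is a 7-site, 2-group, parallel RCT with a treatment versus control allocation ratio of 3:2". The Abstract and Study Setting also give 7 sites, and the covariate list under Statistical Analysis Models numbers high schools 1 to 7.

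**The concern.** For a given sample size, power, alpha and control rate there is one minimum detectable effect on a given scale. The section gives two, 0.24 and 0.2, both called Cohen's d and both placed beside odds ratios. The reasons offered for the choice of effect point to values below the one that produced the sample size, so they do not support 508/339.

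The enrollment target has a separate problem: its per-site figure and its total cannot both be right for a 7-site trial.

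Both figures matter for reading the result. Recruitment closed at 533 (Results), and Limitations reports lower enrollment than expected. A null or imprecise result will be judged against the planned detectable effect and the planned size. The 533 randomised are 62% of 865 (533/865) but 44% of 1,211 (533/1,211).

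**Working it through.** **Inputs.** From Power Analyses: difference 0.09, prevalence ratio (PR) 0.74, two-sided 5%, power 80%, ratio r = 1.5 (intervention to control), 508/339. The control rate is not stated and is derived in step 1.

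**1. Implied rates.** Control p_c = 0.09/(1 − 0.74) = 34.6%; intervention p_t = 25.6%. These give OR 0.650 and d = |ln(OR)|·√3/π = 0.237, matching the stated 0.65 and 0.24. They also reproduce the stated interval. SE of ln(PR) = √[(1−p_t)/(508·p_t) + (1−p_c)/(339·p_c)] = 0.106, so the 95% CI is exp(ln 0.74 ± 1.96 × 0.106) = 0.60 to 0.91. A control rate near 35% is therefore well supported, though it is an inference.

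**2. The stated sample size.** With p̄ = (p_c + r·p_t)/(1 + r),

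n_c = [1.960·√((1+1/r)·p̄(1−p̄)) + 0.842·√(p_c(1−p_c) + p_t(1−p_t)/r)]² / (p_c − p_t)²

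- 35% vs 26%: p̄ = 0.296; n_c = (1.155 + 0.502)²/0.0081 = 339; intervention 1.5 × 339 = 508.5. This matches.
- 34.6% vs 25.6%: n_c = 337; 508/339 has 80.3% power.

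The smallest odds-ratio effect with 80% power at 508/339 is OR 0.651, d = 0.236.

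**3. The conversion in use.** OR 0.65 gives 0.237 (stated 0.24) and OR 0.70 gives 0.197 (stated 0.19). Both stated values are consistent with d = |ln(OR)|·√3/π, so on this scale OR = exp(−d·π/√3).

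**4. Power of 508/339 on that scale, control rate 34.6%.**

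| d | OR | Intervention rate | Power |
|---|---|---|---|
| 0.24 | 0.647 | 25.5% | 81% |
| 0.20 | 0.696 | 26.9% | 67% |
| 0.19 | 0.708 | 27.3% | 62% |
| 0.15 | 0.762 | 28.7% | 44% |

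For d=0.2 the difference is 7.7 points. Power is 63%, 67% and 70% at control rates of 30%, 35% and 40%. For 80% power, n is 467 control and 701 intervention (1,168) at a control rate of 34.6%, or 464 and 696 (1,160) at 35%.

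**5. The same 9 points on other scales.** Cohen's h = 2·arcsin√p_c − 2·arcsin√p_t = 0.197 (0.196 for 35% vs 26%), and difference/SD is about 0.197. The standardised difference detectable at 80% power is (1.960 + 0.842)·√(1/339 + 1/508) = 0.196, and power for 0.20 is 81%.

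**6. Enrollment target.**
- 173 per site over 5 semesters is 173/5 = 34.6 per semester, which agrees with the stated 34 to 35.
- 865/173 = 5 sites exactly.
- 7 × 173 = 1,211.
- 865/7 = 123.6 per site, or 123.6/5 = 24.7 per semester.

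**The case against.** The strongest reply is that nothing is wrong with the sample size. The figures 508/339 are correct for a 9-point difference, and the section ties its 80% to that difference and prints d=0.24 beside it. On Cohen's h or difference/SD, 9 points is about 0.2, so the two paragraphs may describe one design on two scales, and the 67% would then not apply.

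Most of this stands. The calculation is sound, and the 67% is conditional on the odds-ratio scale. But the reply does not make the text consistent. The section labels the 9 points d=0.24 and supports d=0.2 with an odds ratio converted to d=0.19, so the only scale it shows is the odds-ratio one. If two scales were mixed, that is what needs correcting.

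On enrollment, the total of 865 lies just above the required 847, so it is coherent as a total and 533 can be read against it. That is fair, and it suggests that the per-site breakdown is the part at fault. A plan first made for five sites would explain the figures, but the article does not say so. The word approximately cannot cover the gap between 865 and 1,211.

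A reader might also infer from the closeness of 865 and 847 that no allowance for loss to follow-up was made. The article neither states nor denies one, and a condensed article may leave this to the full protocol, so the inference is not supported.

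**Conclusion.** Two inconsistencies stand.

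First, the minimum detectable effect stated in the rationale (d=0.2) is not the effect for which 508/339 was calculated (d=0.24). On the section's own conversion the planned sample has about 67% power for d=0.2. This assumes a control prevalence of about 35%, which is inferred from 9 points and PR 0.74; the range is 63% to 70% for control rates of 30% to 40%. If 0.2 is on Cohen's h or difference/SD, power is about 81% and the fault is one of labelling. The article does not settle which was meant, so it would go too far to say that the planned sample lacked 80% power for the authors' intended effect, or that the sample size was miscalculated.

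Second, the enrollment target of 173 per site and 865 in total is consistent only with 5 sites, while the trial has 7. This needs no assumption. Which of the two figures is correct cannot be told from the article.

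**What to change.** In Power Analyses, give one minimum detectable effect, name its scale, and state the control prevalence assumed. If d is on the odds-ratio scale, say that 508/339 gives 80% power for d=0.24 and about 67% for d=0.2, and describe d=0.2 as the effect of interest rather than the minimum detectable effect. If 0.2 was meant as Cohen's h or difference/SD, say so and remove the mixed labels.

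In Baseline Data Collection, state how many sites the target assumed, so that the per-site figure and the total agree: 5 sites at 173 each, 7 sites at about 124 each (about 25 per semester) for 865, or a total of 1,211 if 173 per site was intended for all 7.

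The cost is a correction to two sections. Recruitment is closed, and neither conduct nor analysis changes. On the odds-ratio reading, the stated power becomes somewhat less favourable.
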